
### Intra-operative variables

The following variables will be collected from the anaesthetic record, operation report, and medical record: duration of anaesthesia during surgery in minutes; mechanical ventilation parameters including mode of ventilation, level of pressure/volume control, and PEEP; average FiO_2_ during surgery; type and amount of intraoperative fluid delivered (ml/kg/h); numbers of blood transfusion units; prophylactic antibiotic delivery (medication and dosage); incision type (midline, unilateral subcostal, bilateral subcostal, transverse, combined thoracotomy, other). If there are multiple incisions used, the patient’s incision is categorised according to the closest abdominal incision to the thorax.

### Post-operative variables

Post-operative data will be collected daily for 14 days or until discharge from hospital, whichever occurs first: time in days from the pre-operative physiotherapy session to the operation; PPC risk stratification (low or high) using a defined risk calculation tool [5]; location (ICU, surgical ward, other) and duration in days at each location; days of analgesia and type (epidural, constant opioid infusion, patient controlled analgesia (PCA), patient controlled epidural analgesia (PCEA), oral, local pain infusion, or other); unplanned ICU/HDU admission and length of total ICU/HDU stay; length in days of total hospital stay; hours of mechanical ventilation; fluid delivery in the first 24 h (ml/kg/h); days and type of vasopressor use; hours and type of NIV use; days and types of oxygen therapy use; days, type, and indication for use for antibiotics; days and types of all drains and lines; day and diagnosis of a prolonged post-operative ileus using a standardised criteria [71] of 2 or more of the following factors in a 24-h period including nausea/vomiting, inability to tolerate normal diet, absence of flatus, abdominal distension, radiologic confirmation, and physician diagnosis of ileus.

Early ambulation parameters will be collected, including: time in hours from end of surgery until time to ambulation >1 min; post-operative day walked longer than 10 min; maximum rating of perceived exertion during ambulation at each session; maximum ambulation stage attained at each session (Table 2); number of assisted ambulation occasions; reasons for a patient being unable to participate in an ambulation session.

### Sample size

Sample size was calculated using inference for proportions comparing two independent samples with a 0.05 two-sided significance level and will have 80 % power to detect a 10 % absolute difference in PPC between Pre-Op (estimated at 10 %) and an education booklet (estimated at 20 %) when the sample size is 398. This is further increased by 11 % to account for attrition, resulting in a final sample size of 441.

### Data management

Data will be collected from participants using a standardised electronic case report form (CRF) and stored in participating centres’ password protected electronic hard drives. To ensure data quality the CRF has been designed with extensive use of data entry limitation rules and on-screen prompts to ensure correct data entry. Primary and secondary outcome data entry fields will be highlighted and required for completion of each participant’s data set. Automated weekly prompts will remind site investigators to complete any missing data points.

All site investigators will be trained directly by the principal investigator on correct administration of the trial. Site investigators will be required to perform random covert audits of data collected by trial personnel during the trial for reliability and correctness against the medical record. Once each participant’s data set is completed, it is de-identified, entered into a central database, and maintained securely by the principal investigator. All data, consent forms, and relevant correspondence will be stored according to Australian and New Zealand privacy laws and archived at trial sites for a minimum of 7 years. There are no industrial contractual arrangements in relation to the de-identified data. On completion of the trial, the database will be made available for independent analysis or as an appendix in the publishing journal if requested.

### Statistical methods

The prognostic strength and size of imbalances to potential confounding baseline variables between groups will be assessed. Adjustment covariates will be selected by backward stepwise regression from covariates that may have the potential for clinically significant alterations in effect sizes. These include: history of a respiratory comorbidity, smoking history, self-reported physical activity levels, age, BMI, length in time of operation, operation category (upper gastrointestinal, colorectal, urological, other), ICU admission immediately following the procedure, incision type and location [72], intraoperative ventilation strategies [4, 73], fluid delivery [74], blood transfusions [75], mode of post-operative analgesia [76], and use of prophylactic antibiotics [50].

All outcomes are to be analysed using intention-to-treat. The absolute and relative rates of PPC in the trial groups will be estimated using multivariate robust random effects Poisson generalised linear regression to allow assessment of binary outcomes with or without adjustment for potential confounding variables (incidence rates and rate ratios, 95 % confidence intervals, *P*-values). Treatment centre will be treated as a fixed variable in the multi-level models. In addition, the effect of time from the end of surgery/anaesthesia to commencement of symptoms of PPC will be compared using Cox proportional hazards regression with and without covariate adjustment (hazards ratio, 95 % confidence intervals, *P*-values). Graphic representation of this analysis will be performed using the Kaplan-Meier method.

Binomial secondary outcomes, including pneumonia, unplanned ICU admission, and patient reported complications, will be analysed using mixed effects Poisson regression. Secondary outcomes with irregular distributions, including length of time periods (ICU and total post-operative LOS, time to ambulation for 1 and 10 min, and time to discharge from assisted ambulation physiotherapy service), HRQoL, and functional capacity, will be evaluated for group differences using mixed effects ordered logistic regression, with mean time (95 % CI) estimated for descriptive purposes using mixed effects linear regression, with or without log transformation depending on distribution. Hospital costs associated with the interventions will be compared using mixed effects linear regression. Log transformation of highly skewed cost data will be performed.

An intention-to-protocol sensitivity analysis will be performed by excluding from the analysis any participant who did not undergo the anticipated scheduled upper abdominal surgery defined as a 5-cm incision or longer above, or extending above, the umbilicus. For example, this will include those participants who were scheduled for open surgery yet went on to only have a laparoscopic procedure or where the open incision remained wholly below the umbilicus.

The sensitivity of the outcome estimates to missing data will be evaluated using multiple imputation (Stata command syntax mi). All analyses will be performed using Stata version 13 or later (StataCorp, College Station, TX, USA).

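### Adjusters for the PPC model are picked by backward stepwise regression from 14 candidates, at least eight measured after randomisation, and neither the adjusted nor the unadjusted result is named primary

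*Protocol article*

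**What the plan says.** All the wording at issue is in Statistical methods of the protocol article.

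- **Screening step:** "The prognostic strength and size of imbalances to potential confounding baseline variables between groups will be assessed".
- **Selection rule:** "Adjustment covariates will be selected by backward stepwise regression from covariates that may have the potential for clinically significant alterations in effect sizes". No stay threshold and no forced-in terms are given.
- **Candidates:** an inclusive list of 14. It opens with "history of a respiratory comorbidity, smoking history, self-reported physical activity levels, age, BMI, length in time of operation", goes on to operation category and "ICU admission immediately following the procedure, incision type and location", then "intraoperative ventilation strategies", fluids, "blood transfusions", "mode of post-operative analgesia" and prophylactic antibiotics.
- **Primary model:** a robust Poisson regression for PPC that yields rate ratios, confidence intervals and P-values "with or without adjustment for potential confounding variables", with centre as a fixed variable. The Cox model for time to PPC is likewise planned both ways.

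The article nowhere says which version carries the trial's conclusion.

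**The concern.** Three features act together.

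1. **No single primary result.** Two P-values for the same hypothesis are planned at a two-sided 0.05 level. If they fall on different sides of 0.05, the protocol gives no rule for which one counts.
2. **Data-driven adjustment.** Backward stepwise regression uses the trial's own outcomes to decide which terms stay, and the reported P-value and interval then take no account of that search. Keeping the statistician blind to group labels does not remove this, because the selection still uses the outcome data.
3. **Post-randomisation candidates.** A variable that arises after allocation cannot confound a randomised comparison. If the session influences it, adjusting for it removes part of the effect that the trial sets out to estimate.

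At stake is whether the headline rate ratio estimates the whole effect of the session, and whether its P-value has the stated error rate.

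**Working it through.** **Step 1: timing of the candidates.** Randomisation and allocation places the opening of the envelope after consent and before the pre-operative session. Trial setting puts the clinic one to six weeks before surgery, and Standardisation of pre-operative interventions requires even late or telephone enrolment to precede surgery. Anything filed as intra- or post-operative is therefore post-randomisation.

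| Candidate | Filed under | Before randomisation? |
|---|---|---|
| Respiratory comorbidity, smoking, physical activity, age, BMI | Pre-operative variables | Yes (5) |
| Operation category | Pre-operative variables, if the planned category is meant | Yes (1) |
| Duration of surgery, incision, ventilation, fluids, transfusion, prophylactic antibiotics | Intra-operative variables | No (6) |
| Immediate ICU admission, post-operative analgesia | Post-operative variables | No (2) |

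The total is 5 + 1 + 6 + 2 = 14, of which 6 + 2 = 8 are post-randomisation. The count is 9 if operation category means the operation actually performed.

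**Step 2: the plan's own sample size.** Inputs from Sample size: 20 % v 10 %, two-sided alpha 0.05, power 80 %. With pooled variance and no continuity correction:

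n per arm = [1.96 × √(2 × 0.15 × 0.85) + 0.8416 × √(0.20 × 0.80 + 0.10 × 0.90)]² / 0.10² = (0.990 + 0.421)² / 0.01 ≈ 199

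The total is 398, as stated. The calculation is a plain two-group comparison with no covariates.

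**Step 3: information available for selection.** Expected PPCs = 199 × 0.20 + 199 × 0.10 = 59.7. Per candidate, 59.7 / 14 = 4.3. If the multi-level candidates are dummy-coded to 25–31 parameters (an assumption about coding), the figure is 59.7 / 25 = 2.4 to 59.7 / 31 = 1.9.

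**Step 4: type I error by simulation.** 398 patients, no treatment effect, robust Poisson, treatment forced in, backward elimination. The stay thresholds, number of candidates and covariate strengths are assumptions, because the protocol gives none.

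| Scenario | Unadjusted | Fixed six-covariate model | Stepwise-adjusted | Either may be claimed |
|---|---|---|---|---|
| 14 candidates, stay P < 0.10, 4000 replicates | 4.7 % | not run | 5.6 % | 6.6 % |
| 25–30 candidates, stay P < 0.10 to 0.20, 4000 replicates | 5.3 % | 5.3 % | 5.9 % | 7.4 % |
| As above, 2500 replicates | 5.1 % | 5.3 % | 7.0 % | 8.5 % |

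The Monte Carlo standard error near 5 % is √(0.05 × 0.95 / 4000) = 0.34 points, or 0.44 points with 2500 replicates. The 25–30-candidate runs had about 69 events, somewhat more than the 60 planned.

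**Step 5: bias if one perioperative covariate is affected.** Assume a binary covariate that doubles PPC risk and has 30 % prevalence in controls.

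- *Session lowers it to 15 %, direct rate ratio 0.60.* Total effect = 0.60 × (1 + 0.15) / (1 + 0.30) = 0.53. Simulated: 0.52 unadjusted and 0.59 stepwise-adjusted; power 74 % v 57 %.
- *Session lowers it to 20 %, direct rate ratio 0.55.* Total effect = 0.55 × 1.20 / 1.30 = 0.51. Simulated: 0.50 unadjusted and 0.54 stepwise-adjusted; power 80 % v 72 %.

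In both cases the adjusted model returns roughly the direct effect and the unadjusted model the total effect.

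**The case against.** **The unadjusted estimate is also planned.** It is protected by randomisation and matches the sample-size calculation. This stands. A reader might infer that the trial's main estimate is unprotected, or that the adjusted model is the primary one. The article says neither; the fault is that it does not choose.

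**The selection rule is easily misread.** A reader might infer that covariates are kept according to how far they move the treatment effect. The phrase about alterations in effect sizes describes the candidate pool; the stay rule of the stepwise procedure is not given. The reference to baseline variables likewise sits in a separate sentence about imbalance, and the Discussion calls the same kind of items perioperative confounders.

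**Mediation is not shown.** Under Blinding, surgeons, doctors and ward staff do not know the allocation, and Standardisation of post-operative procedures leaves anaesthesia, ventilation, fluids, antibiotics and pain management to routine practice. A single education session is unlikely to change incision, ventilation or transfusion. This largely stands: bias needs an effect on the covariate, and that is most plausible for analgesia mode. The rate ratios in Step 5 rest on assumed shifts.

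**Intention-to-treat.** A reader might infer that the adjustment contradicts it. It does not, since nobody is excluded or reassigned. Conditioning on a variable affected by treatment targets a different effect, which is a narrower point.

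**This belongs in an analysis plan.** The stay threshold fairly does, and the primary version might be named there. But the article itself fixes the stepwise method and the mixed candidate list, and those are the badly fixed parts.

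**The inflation is small.** It is. In one run the stepwise excess over unadjusted was 5.9 − 5.3 = 0.6 points, under two Monte Carlo standard errors. The direction is the same in all three runs.

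**Conclusion.** The point holds in a limited form. The adjusted PPC estimate rests on stepwise selection from a list of 14 that mixes six pre-randomisation variables with eight (possibly nine) later ones, with about 60 expected events. The protocol does not say whether that estimate or the unadjusted one decides the trial. That lack of a named primary result, together with the mixed candidate list, matters more than the simulated inflation.

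The inflation is modest: about 6–7 % for the stepwise-adjusted test and about 7–8.5 % if either result may be claimed, against a nominal 5 %. These figures depend on assumed thresholds, candidate numbers and covariate strengths. Bias from perioperative adjustment is possible but not established; its size depends on how far the session changes the covariate, for which the document gives no figure.

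**What to change.** Amend Statistical methods before unblinding (Trial status reports that enrolment continues):

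1. Name one primary analysis of PPC. Either option answers the concern: (a) unadjusted apart from centre, which is closest to the sample-size calculation; or (b) adjusted for centre plus a short fixed list of variables known before randomisation and already collected, for example age, respiratory comorbidity, smoking, BMI and planned surgical category. Report the other version as a sensitivity analysis.
2. Delete stepwise selection, and selection by observed imbalance, for the treatment-effect estimate.
3. Label any model containing intra- or post-operative variables exploratory, and report those variables by arm. This still meets the aim in the Discussion of evaluating perioperative factors.
4. If operation category is used, state that it is the planned category.

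The change is to wording only. It needs no extra data and leaves 398 evaluable and 441 recruited as they are. The cost is that the team gives up choosing adjusters after seeing the data.

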### Primary outcome

The primary outcome is the development of a PPC within the first 14 post-operative hospital days. PPCs will be diagnosed with the Melbourne Group Scale (MGS) diagnostic scoring tool, which is reliable and valid following UAS and thoracic surgery [5, 8] and has high inter-rater reliability [64]. This tool has eight clinical criteria: four factors relating to symptoms and four to diagnostic markers (Table 5). A PPC will be diagnosed when four or more factors are present from midnight to midnight on one post-operative day.

**Table 5 Tab5:** MGS PPC diagnostic criteria with modifications*

Diagnosis confirmed when four or more of the following are present:
Clinical factors
• New abnormal breath sounds on auscultation different to pre-operative assessment • Production of yellow or green sputum different to pre-operative assessment • Pulse oximetry oxygen saturation (SpO_2_) <90 % on room air on more than one consecutive post-operative day • Raised maximum oral temperature >38 °C more than one consecutive day
Diagnostic factors
• Chest radiograph report of collapse/consolidation. *When a CXR has been taken but no report is available, a ward medical officer or a senior respiratory physiotherapist with more than 10 years’ experience will be asked to report • An unexplained WCC greater than 11 × 10^9^/L • Presence of infection on sputum culture report • Physician’s diagnosis of *pneumonia, URTI, or an undefined chest infection, or prescription of an antibiotic for a respiratory infection

* modification made to original criteria

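### Time to PPC is planned with Kaplan-Meier and Cox although PPC can be recorded only in hospital; if discharge is censored, the curve overstates in-hospital incidence

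*Protocol article*

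**What the plan says.** Under Primary outcome, the protocol article defines an in-hospital event: "The primary outcome is the development of a PPC within the first 14 post-operative hospital days". Under Post-operative variables it sets the end of observation: "Post-operative data will be collected daily for 14 days or until discharge from hospital, whichever occurs first". After discharge, Secondary trial outcomes lists only patient-reported complications, quality of life and functional capacity at 6 to 8 weeks, so a PPC on the Melbourne Group Scale cannot be recorded once the patient has gone home.

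Statistical methods compares PPC rates by robust Poisson regression on the binary outcome. As an addition, it compares time from the end of surgery or anaesthesia to the start of PPC symptoms by Cox regression, and "Graphic representation of this analysis will be performed using the Kaplan-Meier method". The article gives no rule for discharge or death before day 14 in that analysis and names no competing-event method.

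**The concern.** Kaplan-Meier and Cox handle a patient who leaves observation by assuming that the patient's later risk equals that of those still observed. Discharge does not fit that assumption. Patients go home because they are well, and after discharge an in-hospital PPC can no longer happen. For this endpoint discharge is a competing event, and so is death.

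If PPC-free patients are censored at discharge, each later PPC is divided by a shrinking group of patients still in hospital. The complement of the Kaplan-Meier curve then rises above the proportion who had a PPC in hospital. The primary analysis keeps the same patients in its denominator as non-events. One endpoint could thus appear in the report with two different day-14 incidences and no explanation. Length of stay is itself a secondary outcome, so the distortion could also differ between arms.

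**Working it through.** **The plan's own figure.** Inputs from Sample size: "0.05 two-sided significance level", "80 % power to detect a 10 % absolute difference in PPC", PPC 20% with the booklet and 10% with the session, "when the sample size is 398". With pooled variance and 1:1 allocation (assumed), n per arm = [1.960·√(2·0.15·0.85) + 0.842·√(0.16 + 0.09)]² / 0.10² = 199, so 398 in total, with power 80.0%. Adding 11% gives 398 × 1.11 = 441.8, against 441 stated. The figure reproduces. It is a comparison of two proportions and does not depend on the time-to-event analysis.

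**What is not in the document.** It gives no distribution of PPC onset or length of stay. Everything below rests on assumed inputs and shows a range, not an estimate for this trial.

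**Check A: daily recursion over days 1 to 14.** Let R be the fraction still in hospital without a PPC (R₀ = 1), h the daily PPC hazard and r the daily discharge probability.
- PPCs on day d: e = R·h
- Discharges on day d: c = (R − e)·r
- Carried forward: R − e − c
- In-hospital incidence = Σe; Kaplan-Meier complement with censoring at discharge = 1 − Π(1 − h)

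With a flat h of 2%, the complement is 1 − 0.98¹⁴ = 24.6% whatever the discharge pattern. With an early-peaked hazard (5, 5, 4, 3, 2, 1 and 0.5% on days 1 to 7, then 0.1% a day) it is 19.4%.

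| Discharge pattern | Flat: in-hospital / KM | Excess (points) | Early: in-hospital / KM | Excess (points) |
|---|---|---|---|---|
| 10%/day from day 6 | 20.0% / 24.6% | 4.7 | 19.2% / 19.4% | 0.3 |
| 15%/day from day 5 | 17.0% / 24.6% | 7.6 | 18.9% / 19.4% | 0.6 |
| 20%/day from day 5 | 15.6% / 24.6% | 9.1 | 18.7% / 19.4% | 0.7 |
| 20%/day from day 4 | 14.0% / 24.6% | 10.6 | 18.2% / 19.4% | 1.3 |

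(Excesses are taken before rounding.) In relative terms the overstatement is 1.23 to 1.76 times with the flat hazard and 1.01 to 1.07 times with the early one.

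**Check B: in-hospital incidence fixed at the design values.** True incidence is 20% (control) and 10% (intervention). Assumed onset is lognormal with median 2, 3 or 5 days (log-SD 0.6). Assumed discharge of PPC-free patients is lognormal with median 6, 8 or 10 days (log-SD 0.5). The Kaplan-Meier complement is 1 − Π(1 − e/R), with e the PPCs on each day and R those still in hospital without a PPC.

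| Onset median, stay median | Control (true 20%) | Intervention (true 10%) |
|---|---|---|
| 2 d, 10 d (smallest excess) | 20.4% | 10.2% |
| 3 d, 8 d (middle) | 22.9% | 11.5% |
| 5 d, 6 d (largest excess) | 41.1% | 22.2% |

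The excess runs from 0.4 to 21 points in the control arm and from 0.2 to 12 points in the intervention arm.

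**Differential stay.** In the middle case, if PPC-free patients in the intervention arm alone stay one day less, that arm's complement moves from 11.5% to 12.3%. The ratio read from the curves falls from 22.9/11.5 = 1.99 to 22.9/12.3 = 1.86, although the true ratio is still 2.

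**The alternative handling.** If discharged patients stay in the risk set event-free to day 14, or discharge is a competing event in a cumulative incidence function, the day-14 values in Check B are exactly 20% and 10%.

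**The case against.** The strongest objection is that the article never says discharge is a censoring event. Post-operative variables says when data collection stops, not how a discharged patient enters the risk set. The endpoint definition makes a patient discharged without a PPC a known non-event, so carrying that patient to day 14 fits the text as well, and Kaplan-Meier with that risk set is unbiased for in-hospital incidence. The rule may also stand in a full protocol or SAP that is not shown. This stands, and the point is therefore conditional. What remains is that the article names estimators whose ordinary use, with observation ending at discharge, gives the wrong incidence.

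Four stronger readings are tempting, and the document does not support them.

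- *The curve will contradict the primary result.* The plan announces a hazard ratio and a graph, not a day-14 Kaplan-Meier estimate, and the excess may be too small to notice.
- *The overstatement is at least 11% in relative terms.* The early-peaked hazard above gives 1% to 7%, so 11% is no floor. Daily assessment only to day 7, then on clinical suspicion, may suggest that early onset was expected, but the article does not say so.
- *The trial hypothesises that the session shortens stay on its own account.* Trial objectives only evaluates the effect on stay, and the Discussion links better recovery to fewer PPCs. A case with equal PPC hazards and discharge at 15% against 20% a day from day 5 gives in-hospital incidences of 17.0% against 15.6%, but no section proposes that mechanism.
- *The Cox ratio is wrong.* With discharge censored it is a cause-specific hazard ratio, which is a legitimate estimand. That it need not equal the risk ratio is a general property, and the Poisson model already supplies the risk comparison.

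**Conclusion.** The point holds conditionally. PPC is observable only in hospital, observation ends at discharge, and the article plans Kaplan-Meier and Cox without treating discharge or death as competing events. If PPC-free patients are censored at discharge, the curve overstates in-hospital PPC incidence in every scenario tried and need not agree with the binary primary result.

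The size depends wholly on assumed onset and stay: under 1 point with early onset and long stay, about 8 to 11 points with a flat 2% daily hazard and early discharge, and up to 21 points in the most extreme lognormal case. If discharged patients are kept to day 14, the excess is zero.

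The matter is confined to a supplementary analysis. The primary Poisson comparison and the sample size of 398 (441 with attrition) are untouched. It is worth correcting because a reader will take incidence off the figure.

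**What to change.** State how discharge and death before day 14 enter the time-to-PPC analysis, and choose one of two displays:

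1. Aalen-Johansen cumulative incidence curves by arm, with discharge and death without a PPC as competing events; or
2. Kaplan-Meier curves in which participants discharged without a PPC stay event-free in the risk set to day 14, with deaths before a PPC handled as in the primary analysis, so that the curve ends at the primary endpoint's proportion.

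If the Cox model censors at discharge, label its hazard ratio cause-specific. A subdistribution hazard ratio beside it is optional.

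The cost is a sentence or two of text and a few lines of Stata. Length of stay is already collected, so no new data are needed, and the sample size and primary analysis do not change.

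### Robust variance is named for the primary binary outcome but not for the binary secondary outcomes; read literally, their Poisson standard errors would be too large

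*Protocol article*

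**What the plan says.** The Statistical methods section of the protocol article defines the PPC analysis as "multivariate robust random effects Poisson generalised linear regression to allow assessment of binary outcomes". The paragraph that follows turns to the yes/no secondary outcomes and states: "Binomial secondary outcomes, including pneumonia, unplanned ICU admission, and patient reported complications, will be analysed using mixed effects Poisson regression".

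The word robust appears in the first description and not in the second. Nothing in the rest of the section, including the text on the sensitivity analysis and on missing data, extends it to the secondary outcomes. On centre, the section says: "Treatment centre will be treated as a fixed variable in the multi-level models".

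The article gives planning rates for PPC only. It gives no expected rate for pneumonia, unplanned ICU admission or patient-reported complications.

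**The concern.** Poisson regression with a log link is a sound way to estimate a rate ratio for a yes/no outcome, provided that the variance is corrected. The Poisson likelihood sets the variance equal to the mean, p, whereas a yes/no outcome has the smaller variance p(1−p). Without a sandwich correction the standard error is too large, and more so as the event becomes more frequent.

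An analyst who follows the text to the letter would therefore use two variance estimators for the same kind of variable, with no reason given. For the three secondary outcomes, intervals labelled 95 % would cover more than 95 %, the tests would run below the nominal 5 %, and a real difference in either direction would be somewhat harder to show.

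**Working it through.** **Inputs.** From the Sample size section: "0.05 two-sided significance level"; "80 % power to detect a 10 % absolute difference in PPC"; planning rates of 10 % (intervention) and 20 % (booklet); 398 evaluable patients. Assumed here: equal allocation, so 199 per arm, and event rates from 2 % to 50 % for the secondary outcomes.

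**Step 1: the plan's own figure.** With pooled variance and no continuity correction, n per arm = [1.96·√(2·0.15·0.85) + 0.8416·√(0.20·0.80 + 0.10·0.90)]² / 0.10² = (0.990 + 0.421)² / 0.01 ≈ 199. Two arms give 398, as stated. That figure is not in question; it fixes the sample size for what follows.

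**Step 2: the two variances of the log rate ratio.**

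- Model-based Poisson: 1/(n₁p₁) + 1/(n₂p₂)
- Correct for yes/no data, and the target of the sandwich estimator: (1−p₁)/(n₁p₁) + (1−p₂)/(n₂p₂)

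With equal rates in the two arms the ratio of standard errors is 1/√(1−p), and the actual two-sided type I error is 2·[1 − Φ(1.96/√(1−p))].

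**Step 3: size under no treatment effect.**

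| Assumed rate | Model SE / correct SE | Actual type I error | Actual coverage of a 95 % interval |
|---|---|---|---|
| 2 % | 1.01 | 4.8 % | 95.2 % |
| 5 % | 1.03 | 4.4 % | 95.6 % |
| 10 % | 1.05 | 3.9 % | 96.1 % |
| 20 % | 1.12 | 2.8 % | 97.2 % |
| 30 % | 1.20 | 1.9 % | 98.1 % |
| 40 % | 1.29 | 1.1 % | 98.9 % |
| 50 % | 1.41 | 0.6 % | 99.4 % |

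**Step 4: power.** Let SE_r be the correct standard error and SE_m the model-based one. Power is Φ(|log RR|/SE_r − 1.96) with robust variance and Φ((|log RR| − 1.96·SE_m)/SE_r) without. For 20 % against 10 %: SE_r = √(0.80/39.8 + 0.90/19.9) = 0.256 and SE_m = √(1/39.8 + 1/19.9) = 0.275, which gives 77 % and 73 %. (The 77 % differs from the planned 80 % because this is a Wald test on the log ratio, not the pooled test of a difference.)

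| Assumed rates | Power, robust | Power, model-based |
|---|---|---|
| 6 % vs 3 % | 29 % | 28 % |
| 10 % vs 5 % | 46 % | 43 % |
| 20 % vs 10 % | 77 % | 73 % |
| 40 % vs 30 % | 54 % | 37 % |
| 50 % vs 35 % | 85 % | 66 % |

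**Step 5: simulation.** Poisson regression with centre as a fixed effect, 398 patients, no treatment effect, 1,500 runs per rate.

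- At 20 %: empirical SD 0.207, mean model SE 0.227, mean robust SE 0.203; rejection 2.5 % model-based, 4.5 % robust.
- At 50 %: empirical SD 0.103, mean model SE 0.142, mean robust SE 0.100; rejection 0.6 % model-based, 6.0 % robust.

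With 1,500 runs, a true 5 % rejection rate has a simulation standard error of √(0.05·0.95/1500) = 0.6 %, so 4.5 % and 6.0 % are both compatible with 5 %.

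**Step 6: does the mixed-effects part repair this?** No. A random effect can only add variance to the Poisson model, and here the Poisson variance is already too large.

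**The case against.** The strongest reply is that the article omits a qualifier and does not state an error. Nowhere does it say that model-based standard errors will be used. The robust model is introduced one paragraph before, and its purpose is given in general terms, for binary outcomes in the plural. Authors who know why Poisson regression needs a robust variance probably meant the same model when they named it more briefly, and an article condenses. This stands in part: it rules out saying that the standard errors will certainly be wrong. It does not remove the point. The article does name the model for these outcomes, and the model as named has the defect.

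The second reply concerns size. The larger figures need event rates that the article does not give. A reader might infer that patient-reported complications will be common, or that the plan in effect discards half the sample. The latter is true only at an assumed 50 % rate, where 1.41² = 2, and nothing in the article supports that rate. A reader might also infer that harm through more ICU admissions would be missed. If that outcome occurs in 10 % of patients or fewer, again an assumption, the standard error is at most about 5 % too large; power at 10 % against 5 % falls only from 46 % to 43 %, and most of the shortfall comes from sample size. These objections are sound.

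Third, the error is conservative. It does not push the false-positive rate above 5 %, and it does not touch the primary outcome. That is also correct.

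**Conclusion.** The point holds on the text as written and is modest. Robust variance is specified for PPC and not for the three binary secondary outcomes. On the literal reading their standard errors are too large by a factor of about 1/√(1−p): negligible to small at rates of 2 to 10 %, 12 % at 20 %, and 41 % at 50 %. Intervals are then too wide, tests conservative, and power is lost mainly for an outcome that proves common. The point estimate is essentially unaffected.

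The sizes rest on assumed event rates, on 199 patients per arm, and on the wording being followed literally and not as shorthand. The article does not support a claim that the reported errors will in fact be wrong, that any particular outcome will be badly affected, or that the primary analysis is at fault.

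**What to change.** In the sentence on binary secondary outcomes, state that participant-level robust (sandwich) variance applies to every such outcome analysed by Poisson regression, with centre entered as the fixed variable that the section already specifies. Participant level should be stated because the Trial setting section lists only three centres, too few clusters for a sandwich estimator clustered on centre. The primary model need not change.

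The cost is a few words in the plan and one software option. No new data or additional patients are needed. If robust variance was intended throughout, the change only makes that explicit.
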